##### Grip Strength

Maximal grip strength will be obtained with a Jamar hydraulic grip strength dynamometer (Performance Health, LLC, Akron, OH USA). Handle position of the dynamometer will be standardized at position II (61). The subject will be seated with the shoulder in neutral position and the elbow supported and flexed to 90° with the forearm and wrist in neutral position. The subject will squeeze the dynamometer handle as hard as possible for 3 s and maximal force will be recorded in kg. The subject will perform three trials with each hand, and 15 s rest will be allowed between trials. Peak force of each hand will be used for analysis. Grip strength will be performed at baseline, after the 24-week training period, and at 4- and 12-weeks post-intervention.

##### Muscle Sympathetic Nerve Activity

Muscle sympathetic nerve activity (MSNA) will be recorded from the common peroneal nerve *via* tungsten microelectrode (200 μm: 25–40 mm, impedance: 5 MX) (FHC, Bowdoin, ME) inserted percutaneously immediately posterior to the fibular head. Due to the technically difficult and time-consuming nature of MSNA, it will be assessed in a subset of subjects in the CHART study (*n* = 10/group). Subjects selected to complete MSNA testing will do so at a visit separate from Visit 1 and Visit 2 at baseline, after the 24-week intervention, and at the 12-week follow-up. Subjects will rest in a chair reclined ~45° with the right knee and foot supported by positioning pillows (VersaForm, Performance Health, Warrenville, IL). Microelectrode placement will be confirmed *via* electrical stimulation (0.02 mA, 1 Hz) as described previously (62, 63). A second microelectrode will be inserted just below the skin surface ~1.0 cm from the first to serve as a reference electrode. Electrode position in sympathetic fascicles will be confirmed by pulse synchronous bursts of activity, elicitation of afferent nerve activity by mild muscle stretch, and absence of response to light stroking of the skin or with startle response to loud noises (62). The recorded signal will be amplified (gain 2 × 10^4^), bandpass filtered (500–2.0 kHz) using a pre-amplifier (NeuroAmp Ex; ADInstruments, Colorado Springs, CO), and signals will be full-wave rectified (100 ms moving window) and sampled at 10 kHz. The resulting signal will be monitored using a computer-based data acquisition and analysis system (LabChart 8.0 software, ADInstruments, Colorado Springs, CO) and loudspeaker throughout the experiment. MSNA will be recorded for 10 min, and bursts that exceed a predetermined threshold will be marked and counted. Outcomes will include bursts/minute, bursts/100 heart beats, and mean burst area/minute.

### Sample Size Calculation and Power

A minimum of 92 and maximum of 122 participants will be enrolled and randomized in this study (*n* = 46–61 per group). As OSA prevalence is 2-fold greater in males than females over the age of 50 (64–66), we expect to enroll males at a 2:1 ratio to females. However, we will not restrict enrollment based on sex.

In our preliminary study (49), the effect sizes (ESs) for SBP, PNE, and 24-h SBP were 2.50, 1.25, and 0.63. The within individual standard deviation (SD) was set to be the larger of the SDs for the two groups, although differences in SDs across groups were not substantial. If 45 participants per arm complete the main study, we will have over 80% power for any outcome with an ES > 0.63. Sex-specific comparisons of mean change scores between IMST groups can detect an ES > 1.19, provided at least 30 females complete the study (i.e., 75% of 1/3 of the initial sample size of 122), with at least 15 in each arm. This calculation includes a Bonferroni correction of the significance level—that is, the sex-specific comparisons are conducted at the 2.5% significance level.

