## Methods

### Study Design

The CHART Study is a Phase II randomized, double-blind, sham-controlled, mechanistic clinical trial comparing high- and low-resistance IMST in 122 MA/O adults (50–80 years) with OSA. The study is a repeated measures design with assessments at four time points: baseline, post intervention, and at follow-up 4- and 12-weeks post-intervention (Figure 2).

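### The stated minimum of 92 randomised does not fit the 45 completers per arm behind the power statement, if the document's only completion figure (75%) applies to everyone

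*Protocol article*

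**What the plan says.** All the figures below are in the protocol article, under Sample Size Calculation and Power unless another section is named.

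- **Enrolment range:** "A minimum of 92 and maximum of 122 participants will be enrolled and randomized in this study", which is "46–61 per group". The Methods paragraph of the Abstract gives the same range as numbers enrolled. Study Design gives only the upper figure: "comparing high- and low-resistance IMST in 122 MA/O adults".
- **Pilot effect sizes:** "the effect sizes (ESs) for SBP, PNE, and 24-h SBP were 2.50, 1.25, and 0.63". Casual SBP is the primary outcome. Plasma norepinephrine (PNE) and 24-h SBP are secondary.
- **Power statement:** "If 45 participants per arm complete the main study, we will have over 80% power for any outcome with an ES > 0.63".
- **Women:** a detectable ES of 1.19 at the 2.5% level, on condition that 30 or more women complete, 15 in each arm. The 30 is explained as "75% of 1/3 of the initial sample size of 122". This is the only place where a completion rate appears.
- **Test level:** two-sided 5% unless otherwise mentioned (Statistical Analysis), with 1:1 allocation (Randomization, Blinding, and Treatment Allocation).

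**The concern.** The enrolment range counts people randomised, while the power statement counts people who complete. At the lower end the two nearly coincide: 46 randomised per group against 45 completing per arm, which leaves room for one loss per arm. Individual participation lasts about 42 weeks (Study Location and Timeline), and the section itself reckons with 75% completion when it derives the number of women.

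The claims at stake are those that sit close to their limits. The threshold ES of 0.63 is exactly the pilot value for 24-h SBP, so that outcome has little slack. The female-specific comparison depends on 30 completers. If enrolment ended at 92, a reader could carry the power statement over to a trial that, on the document's own completion figure, would not meet the condition attached to it.

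**Working it through.** **Inputs.** Randomised: 92 (46 per arm) to 122 (61 per arm). Completers behind the power statement: 45 per arm. Pilot ES: 2.50, 1.25 and 0.63. Completion: 75%. Women: one third of the sample. Alpha: 0.05 two-sided, and 0.025 for the sex-specific comparisons. The ES is already standardised, so SD = 1.

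**Method.** Two-sample comparison of means with n per arm. The noncentrality is ES × √(n/2). The normal approximation to power is Φ(ES × √(n/2) − 1.960). The t-test result is given beside it and is the one used in the conclusions.

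**Step 1: reproduce the stated figures.**
- n = 45, ES 0.63: 0.63 × √22.5 = 2.988, and Φ(2.988 − 1.960) = 84.8%. The t-test gives 84.0%. This agrees with the stated power of over 80%.
- Women, n = 15 per arm, alpha 0.025: the ES detectable with 80% power is 1.18 (t-test), against 1.19 stated. Power at 1.19 is 80.8%.

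**Step 2: apply 75% completion to both ends of the range.**

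| Randomised | Completers | Per arm | Power at ES 0.63 (t-test) | Power (normal) |
|---|---|---|---|---|
| 122 | 122 × 0.75 = 91.5 | 45.75 | 84.6% | 85.4% |
| 92 | 92 × 0.75 = 69 | 34.5 | 73.2% | 74.4% |

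For the second row: 0.63 × √17.25 = 2.617, and Φ(2.617 − 1.960) = 74.4%. With whole numbers, the t-test gives 72.6% at 34 per arm and 73.8% at 35.

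**Step 3: detectable ES at 80% power.** At 34.5 per arm it is (1.960 + 0.842) × √(2/34.5) = 0.675 by the normal approximation and 0.684 by the t-test. At 45 per arm the t-test value is 0.597.

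**Step 4: retention that 92 would need.**
- For 80% power at ES 0.63, the t-test requires 40.5 per arm, so 41: 40.5/46 = 88% and 41/46 = 89%.
- For the stated condition of 45 per arm: 45/46 = 97.8%.
- Power at ES 0.63 from 46 randomised per arm, by completion rate (t-test): 76.0% at 80% completion, 78.5% at 85%, 80.8% at 90% and 82.9% at 95%.

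**Step 5: women.** From 122: 122/3 × 0.75 = 30.5, which matches the stated 30. From 92: 92/3 × 0.75 = 23, or 11.5 per arm. The detectable ES at alpha 0.025 is then 1.37 (1.40 at 11 per arm, 1.34 at 12), and power at ES 1.19 is 67% (65% at 11, 69% at 12).

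**Step 6: the other outcomes.** At 34 to 35 per arm, power at ES 1.25 (PNE) is above 99.9%. For casual SBP (ES 2.50) it is higher still.

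**Step 7: numbers to randomise at 75% completion.** For 45 completers per arm: 45/0.75 = 60 per arm, 120 in all. For 80% power at ES 0.63: 41/0.75 = 54.7, so 55 per arm, 110 in all.

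**The case against.** The strongest reply is that no printed figure is wrong. Both power statements are conditional on completers, both reproduce, and neither is attached to 92 randomised. That stands. A reader might infer that the document claims over 80% power for 92 randomised, but it does not. It sets a minimum from which the stated condition can hardly be met, which is an inconsistency rather than a false calculation.

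Second, the 75% appears only in the sentence on women and is tied to 122. Applying it to all participants is an inference. It has support, because no other rate is given and 122 × 0.75 lands on the 45-completer target, but it remains an assumption.

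Third, the range might be meant to cover uncertain attrition around a fixed target of about 90 completers: 92 if almost nobody leaves, and about 120 (90/0.75) at 25% loss. That would be coherent, but the text does not say so, and near-complete retention conflicts with the one rate it gives. By the same token, a reader might conclude that 92 is simply the expected number of completers (91.5) printed in the wrong place. The match is suggestive, but the documents do not establish it.

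Fourth, 45 per arm is not itself necessary for 80% power at ES 0.63, since 41 is enough. The 98% retention is what the stated condition needs, not what 80% power needs.

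Fifth, maximum likelihood on available data may recover something from partial completers. Participants with no post-baseline value add little to a comparison of change, and the calculation in the text counts completers.

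**Conclusion.** The inconsistency holds. The minimum of 92 randomised and the condition of 45 completers per arm fit together only at about 98% retention, and the document's one completion figure is 75%. If that figure applies to everyone, stopping at 92 gives about 73% power at ES 0.63 for 24-h SBP instead of over 80%. It also gives a detectable ES of about 0.68, and a female-specific detectable ES of about 1.37 instead of 1.19. With completion of about 88 to 89% or more, 80% power at ES 0.63 is kept.

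The result rests on three assumptions: the 75% holds for men as well as women, one third of participants are women, and the power calculation is a two-sample comparison of completers. The stated figures reproduce under the last of these.

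It would be wrong to read this as an underpowered trial. At the pilot effect sizes the primary outcome and PNE are untouched, and the maximum of 122 supports the power statement. The point should be fixed, as an inconsistency between enrolment and power that affects the secondary and sex-specific claims only.

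**What to change.** Either of two changes resolves it.

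1. State that 122 will be randomised (61 per group) so that about 92 complete at 75% completion, and use the same wording in the Abstract and Study Design.
2. Keep 92 as the randomised minimum and print beside it the retention assumed for the whole sample and the power that follows. At 75% completion this is about 73% at ES 0.63 and a female-specific detectable ES of about 1.37.

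Both are wording changes in the sample size section and the Abstract. The maximum enrolment, the outcomes and the procedures stay as they are. The first option gives up the freedom to stop at 92. The second keeps it, at the price of showing a less favourable power figure for 24-h SBP and for women.

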## Treatment of Subjects

### Study Location and Timeline

All baseline, training, post-assessment and follow up measures will be conducted at the University of Arizona's Clinical and Translational Research Services (CATS) facility. The enrollment period for an individual participant will be ~42 weeks. The timeline for the entire study (i.e., recruitment of first subject to study completion for final subject) will be ~54 months.

Subjects who have been screened will have 6 months from the prescreening date to commence the study. If after 6 months they have not attended the first baseline session, they will be required to undergo prescreening assessments again prior to proceeding to baseline assessments.

Two baseline sessions, spaced at least 24 h apart, will be completed within 14 days. Participants will commence the intervention within 14 days of the second baseline assessment and perform their prescribed exercise at home, 5 days/week for 24 weeks. Post-intervention assessments will be completed within a 14-day period, at least 24 h apart and in week 25 ± 1 week. Follow-up assessments will be performed within a 14-day period, at least 24 h apart at 4 ± 1 weeks and 12 ± 1 weeks after the last post-intervention assessment (Table 2).

**Table 2 T2:** Schedule of events.

	**Baseline**		**Exercise intervention**				**Post**		**F4 and F12**	
	**V1**	**V2**	**Wk 1**	**Wks 2–4**	**Wks 6–22**	**Wk 23**	**V1**	**V2**	**V1**	**V2**
Day (window)	−14–0		1–7	8–28	29–154	147-154	168–182		F4: 203–217 F12: 259–273	
**Screening/baseline**										
Informed consent	X									
Demographics	X									
Medical Hx/physical exam	X									
Inclusion/exclusion	X									
Height/weight	X						X		X	
Vitals	X	X	X	X	X	X	X	X	X	X
Neck circumference	X						X		X	
**Cognitive assessments**										
NIH Toolbox			X			X			
**Surveys**										
CHAMPS	X						X		X
PSQI	X						X		X
ESS	X						X		X
**Exercise sessions**										
Daily exercise			X	X	X	X				
Once-weekly supervised			X	X						
Twice-monthly supervised					X	X				
Weekly text/email			X	X	X	X				
**At-home testing**										
24-h BP		X				X			X
HSAT	X						X	
Actigraphy			X			X		
Sleep/exercise diary			X	X	X	X		
**Functional assessments**										
Casual BP		X						X		X
Spirometry	X						X		X
PI_max_			X	X	X	X	X		X
6MW	X						X		X
Grip strength	X						X		X
**Blood draws**										
PNE		X						X		X
Blood chemistries		X						X		X
**Arterial assessments**								
PWV_CF_	X						X		X
PWV_CF_ with NS		X						X		X
FMD_BA_	X						X		X
FMD_BA_ with NS		X						X		X
FMD_BA_ with vitamin C		X						X		X
EID with SL NTG		X						X		X
**Randomization**		X								

*6MW, six-minute walk; CHAMPS, Community Health Activities Model Program for Seniors physical activity questionnaire; BP, blood pressure; EID, endothelium-independent dilation; ESS, Epworth Sleepiness Scale; F4, first follow-up at 4 weeks; F12, second follow-up at 12 weeks; FMD_BA_, brachial artery flow-mediated dilation; HSAT, home sleep apnea testing; Hx, history; NS, normal saline infusion; NTG, nitroglycerin; PI_max_, maximal inspiratory pressure; PNE, plasma norepinephrine; PSQI, Pittsburgh Sleep Quality Index; PWV_CF_, carotid-femoral pulse wave velocity; SL, sublingual; V, visit. ^†^Surveys completed at home: CHAMPS, PSQI, ESS*.

### Baseline Assessments

Eligible participants who are enrolled into the study will undergo the Outcome Assessments and Internal Control Assessments, found in Table 3, within a period of 14 days. Subjects will be asked to maintain their behavior throughout the study, and we will account for unreported changes with the Internal Control Assessments. Protocols for these assessments can be found in the Supplementary Material.

**Table 3 T3:** Outcome assessments and internal controls.

**Outcome assessments**	**Internal controls**
• Casual BP • 24-h BP monitoring • Blood draw • EDD *via* FMD_BA_ (with and without systemic saline and vitamin C infusion) • EID *via* sublingual nitroglycerin • Arterial stiffness *via* PWV_CF_ • 6MW • NIH Toolbox—cognitive domain • PI_max_ • Resting heart rate • Home sleep apnea testing • Grip strength • MSNA (subset of participants)	• Anthropometrics • Surveys • PSQI • ESS • CHAMPS • Actigraphy • Spirometry • Sleep and physical activity diaries

*Outcome Assessments include primary, secondary, and other outcomes of interest in the CHART study. Internal Controls will be completed to determine consistency of behavior throughout the study and to account for unreported changes. See Supplementary Material for protocols related to Internal Controls. 6MW, six-minute walk distance; BP, blood pressure; CHAMPS, Community Healthy Activities Model Program for Seniors physical activity questionnaire; EDD, endothelial-dependent dilation; EID, endothelial independent dilation; ESS, Epworth Sleepiness Scale; FMD_BA_, brachial artery flow-mediated dilation; PI_max_, maximal inspiratory pressure; PSQI, Pittsburgh Sleep Quality Index; PWV_CF_, carotid-femoral pulse wave velocity*.

### Intervention

Following baseline assessments, participants will begin the training intervention. All training will be performed on the POWERbreathe™ K3 trainer (POWERbreathe™ K3, POWERbreathe International Ltd., Warwickshire, ENG), a handheld pressure-threshold device that can: (1) be pre-programmed to provide the appropriate resistance to inspiration, and (2) record data from all training sessions. Each participant will be provided their own device on which to perform their prescribed exercise at home, 5 days/week for 24 weeks, and will receive verbal and written instruction on the training protocol and K3 operation from the unblinded Research Technician.

The Research Technician will supervise the subject's first training session to ensure proper technique and comprehension. In training weeks 1–3, participants will perform 5 training sessions per week; one training session will be supervised by the Research Technician in the CATS facility, and 4 training sessions will be performed unsupervised at home. In training weeks 4–24, participants will perform training sessions unsupervised at home returning to the CATS facility for supervised training sessions twice monthly. At each visit, the unblinded Research Technician will determine the participant's casual BP, collect sleep and activity logs, transfer saved training data from the K3 device, and record any changes in medications, diet, exercise, and/or health status since the previous visit. The participant will complete 3 PI_max_ efforts to establish the following weeks' training level. The new resistance will be set on the K3 using the *Manual* function to ensure that the target resistance remains the same until the next in-person visit. The participant then will perform one supervised training session at this new training level. Subjects will be contacted weekly *via* phone or email to encourage participants and aid in retention and adherence.

Subjects assigned to high-resistance IMST will train against a resistance set at 75% of their PI_max_. Subjects randomly assigned to low-resistance IMST will train against a resistance set at 15% of PI_max_. Subjects in both groups will perform 5 sets of 6 breaths, with 1 min rest between sets, for a total of 30 breaths per day (49). All exercise sessions will be recorded in the device memory card and participants will be required to complete a weekly training log.

### Post Assessments

To determine the chronic effects of IMST and avoid confounding by acute effects of the intervention, two post-intervention assessments will be completed within a 14-day period, at least 24 h apart beginning in week 25 ± 1 week. Participants will continue to perform daily training (except for the days they will be performing post-intervention assessments) until the post-intervention assessments are completed. Post-assessment measurements will encompass all measures obtained at baseline and will be made under the same experimental conditions, at the same time of day, in the same order and with the same techniques as for baseline testing (Table 2).

### Follow-Up Evaluations

Following completion of the post-assessments, participants will return the K3 training device and begin a period of free-living. During this period, subjects will not complete any interventions and will be asked to refrain from making any significant lifestyle changes. Subjects will be contacted weekly *via* phone or email. Primary, secondary, and other outcomes measures will be reevaluated in all participants during follow-up testing after 4 and 12 weeks of free-living. All measurements will be made under the same experimental conditions, in the same order and with the same techniques as for baseline testing, with the exception of home sleep apnea testing which will not be performed at follow-up visits (Table 2).

## Procedures

### Recruitment, Eligibility, and Consent

Recruitment will be *via* newspaper and newsletter advertisement to the general population, University of Arizona (UA) press releases, Facebook, and public presentations to local community groups in the Tucson/Oro Valley/Green Valley region. Once a potential study participant has been identified, they will be directed to the study website where they can complete a questionnaire to determine their eligibility.

Interested candidates will contact the Study Research Professional *via* phone or email (contact information supplied with recruitment materials) and will be asked to complete a general questionnaire online through the Research Electronic Data Capture (REDCap) system to determine eligibility. Information regarding participants' eligibility (whether eligible, ineligible, or withdrawn questionnaires), will be entered into the electronic Screening Log. Questionnaires that do not meet inclusion criteria will be discarded and the candidate will be informed of their ineligibility. Eligible questionnaires will be sent to study physicians for review. Candidates that meet eligibility will be contacted for a study overview session.

Following the study overview, informed consent will be obtained only by members of the research team who have been observed and approved by the Principal Investigator and authorized by the University of Arizona Institutional Review Board (IRB). Written informed consent will be obtained either online *via* REDCap or in person from each subject before the start of any study-related procedures and will be reviewed and signed and dated by the participant and the Study Research Professional in accordance with the Declaration of Helsinki. Ethical Approval for this study has been obtained from the University of Arizona IRB (Protocol #1200000220). We will recruit eligible participants who are able to provide informed consent and who are proficient or independent speakers of English or for whom English is their first language. As such, there is no provision or plan for obtaining consent from speakers of a language other than English.

### Screening Assessment

Participants who have provided informed consent, will undergo screening assessments in Visit 1 to determine whether they meet the enrollment criteria. Screening evaluations will be performed in sequence as follows:

BP measurement: SBP ≥120 mmHg and <160 mmHg, DBP <100 mmHg after 5 min rest in seated position.Physical examination: assessments of the following parameters (jugular venous pressure, cervical lymph nodes, carotid pulse, normal breath sounds, regular heart rhythm, no abdominal swelling/tenderness, no swelling or discoloration of extremities, normal walking/gait, normal arm and leg strength, no rashes).Spirometry in accordance with guidelines from the American Thoracic Society (67): normal (FEV_1.0_) ≥80%.Height and weight measurement: BMI ≤ 40 kg/m^2^.Home sleep apnea test: Apnea Hypopnea Index ≥ 15 events/hour sleep (completed at home after Visit 1 and analyzed before Visit 2).Screening blood chemistries: Total cholesterol <240 mg/dL; Fasting plasma glucose <300 mg/dL.Epworth Sleepiness Scale score <15 (survey completed at home after Visit 1 but before Visit 2).

